##### The primary outcome

2.13.3.1

A linear mixed-effects model (LMM) will analyze the percentage change in real-world targeted extremity movement from baseline (T1) to 12 weeks (T2) and 24 weeks (T3). The model will include fixed effects for Group (Music Motion Feedback vs. Control), Time (T1-T2, T1-T3), and their interaction (Group × Time), adjusted for baseline extremity movement time and sex. A random intercept for each participant will account for individual differences in baseline differences, and a random slope for Time will model variability in improvement rates. If residuals indicate non-normality, a logarithmic transformation will be performed.

Given the moderate sample size, the analysis will be conducted using restricted maximum likelihood estimation. A Holm-Bonferroni correction will be applied to adjust for multiple comparisons. A planned subgroup analysis will evaluate age group effects (adolescents vs. young adults).

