### Randomization

2.6

Participants will be assigned to groups using matched pairs randomization with a 1:1 allocation ratio. Matching will be based on dichotomized ages (adolescents 15–19 years, young adults 20–25 years) and GMFCS-E&R classifications. Within each stratum, participants will be grouped into pairs. A computer-generated randomization sequence will assign the first participant in each pair to either group, with the second assigned to the alternate. [name] will enroll participants and extract age and GMFCS-E&R classifications to create pairs. A third-party allocator will conduct randomization to ensure allocation concealment, with the sequence securely stored and revealed only after statistical analysis is complete.

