#### Primary outcome

2.10.1

The primary outcome is the percentage change in real-world daytime movement of the targeted extremity (right or left arm or leg). We hypothesize this reflects the impact of the anticipated increase in capacity from motor training programs on real-world movement behaviors. Data will be collected from seven IMUs worn by participants for 72 consecutive hours and analyzed using a deep-learning neural network. The methodology details have been previously described [20]. IMUs will be attached with adhesive patches on the sternum, wrists, thighs, and lower legs to collect 3-axis accelerometer and gyroscope data. A custom neural network converts the signals into images and processes them through several convolutional layers, extracting features to recognize movement behaviors. Movement behaviors beyond limb movement will be utilized for exploratory outcomes. Daytime will be recorded in participant logs, noting the times in bed, lights out, devices off, wakefulness, and when they leave bed.

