#### Superiority margin

2.13.1

The change in real-world daytime extremity movement over 72 h from baseline to follow-up (T2) and long-term follow-up (T3) determines the superiority margin, set at a 10 % increase for both upper and lower extremities.

Due to the wide variability in extremity movement among adolescents and young adults with CP at GMFCS-E&R levels I-V (upper: 5.6 %–54.4 %; lower: 1.3 % - 19.4 % of daytime) ([name], manuscript), percentage change was chosen over absolute change. Superiority is claimed if the lower bound of the 95 % confidence interval for the Music Motion Feedback group surpasses the 10 % margin. While no universal threshold for clinically meaningful improvement exists, this margin aligns with chronic stroke findings, where a change of 575–752 accelerometer counts is considered a meaningful improvement (15 %-20 %) [25].

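### The primary mixed model leaves out the two matching factors, age group and GMFCS-E&R level, which makes it conservative and gives up some precision

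*Protocol article*

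**What the plan says.** **Design.** Section 2.6 (Randomization) states: "Participants will be assigned to groups using matched pairs randomization with a 1:1 allocation ratio". It continues: "Matching will be based on dichotomized ages", split at 15–19 and 20–25 years, together with GMFCS-E&R classification. Then: "Within each stratum, participants will be grouped into pairs". One member of a pair is allocated at random and the other goes to the opposite arm.

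**Analysis.** Section 2.13.3.1 (The primary outcome) states: "The model will include fixed effects for Group (Music Motion Feedback vs. Control), Time (T1-T2, T1-T3), and their interaction (Group × Time"), and the model is "adjusted for baseline extremity movement time and sex". On random effects it says: "A random intercept for each participant will account for individual differences in baseline differences", and it adds a random slope for Time. There is no term for age group, GMFCS-E&R level, stratum or pair. Age group returns only as a planned subgroup analysis.

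**Where the model is reused.** Section 2.13.3.2 applies the same approach to the secondary outcomes other than attendance and adherence. Section 2.13.5 adds time since the last BoNT-A injection to the same model.

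**The concern.** Pairing within strata forces the arms to be nearly alike on age group and GMFCS-E&R level. That removes variation in the estimated group difference. A model without those factors does not know that this variation has gone. It leaves it in the between-participant variance and reports a standard error larger than the true sampling SD of the estimate. The participant random intercept does not repair this, because the group contrast is itself a between-participant contrast and its standard error is built on that variance.

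The covariate list is also at odds with the design: sex, which was not a matching factor, is adjusted for, while both matching factors are not. The protocol states this list outright, so it is a rule already set and not a detail left open for the statistical analysis plan.

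At stake are the width of the confidence interval and the chance of detecting a real effect, in a trial planned with little power to spare.

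**Working it through.** **Inputs from the protocol article.** SMD 0.76, 58 analysed (29 per arm), power 81.8%, 70 enrolled (section 2.13.2); 70% of participants projected at GMFCS-E&R I–II (Discussion).

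**Assumptions.** Two-sided alpha 0.05, which section 2.13.2 does not state but which fits the 95% interval in section 2.13.1. R² is the share of outcome variance, beyond baseline and sex, that age group and GMFCS-E&R explain. The documents give no value, so a range that includes zero is used.

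**Step 1: the plan's own figure.** The noncentrality is 0.76 × √(29/2) = 2.894. The normal approximation gives Φ(2.894 − 1.960) = 82.5%, and the noncentral t gives 81.2%. The stated 81.8% lies between them. It is therefore the power of a plain two-group comparison with no gain from covariates.

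**Step 2: closed form with strata perfectly balanced at analysis.** The true SD of the estimate is √(1 − R²) times the unadjusted model's standard error.

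- Type I error without the factors: 2 × P(Z > 1.96/√(1 − R²))
- Power without the factors: Φ((2.894 − 1.96)/√(1 − R²))
- Power with the factors: Φ(2.894/√(1 − R²) − 1.96)

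| R² | Type I error, without | Power, without | Power, with |
|---|---|---|---|
| 0.1 | 3.9% | 84% | 86% |
| 0.2 | 2.8% | 85% | 90% |
| 0.3 | 1.9% | 87% | 93% |

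These figures are an upper bound on the conservatism, because dropout breaks pairs.

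**Step 3: simulation with dropout.** Pairs were randomised within 2 × 5 strata, with 70 randomised and 58 retained at random, in 6,000 runs per setting. The assumed mix was 50/50 for age group and 40/30/12/10/8% for GMFCS-E&R I–V. A linear model was fitted without and with age group and GMFCS-E&R, the latter entered as a linear score.

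| R² | Type I error, without | Type I error, with | Power, without | Power, with |
|---|---|---|---|---|
| 0 | 4.8% | 4.8% | 81% | 81% |
| 0.1 | 4.4% | 5.2% | 81% | 84% |
| 0.2 | 2.9% | 4.3% | 83% | 89% |
| 0.3 | 2.6% | 5.2% | 84% | 92% |

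Monte Carlo error near 5% is √(0.05 × 0.95/6000), about 0.3 points. At R² = 0.3 the mean model-based standard error without the factors is 0.263 against a true SD of 0.232. The ratio 0.263/0.232 = 1.13 means it is about 13% too large.

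**Scope.** All these figures describe a test of the between-group difference against zero. They do not describe the rule in section 2.13.1, which compares a confidence limit with a 10% margin, or the Holm-Bonferroni step in section 2.13.3.1.

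**The case against.** **The size of the loss is unknown.** Nothing in the documents shows that age group or GMFCS-E&R predicts percentage change once baseline movement is in the model. Baseline will absorb part of the GMFCS-E&R differences, and percentage change removes part of the difference in level. This stands: at R² = 0 the omission has no effect, and the size can only be given as a range.

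**The plan still reaches its target.** This also stands. In every row above, power without the factors stays at about the planned level or slightly above. A reader might infer that the trial is underpowered, that its false-positive rate is too high or that the estimate is biased. The documents support none of these. What is given up is additional power and a narrower interval.

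**Dropout softens the effect.** The closed form puts type I error at 1.9% for R² = 0.3, and the simulation with 58 of 70 analysed gives 2.6%. The milder figures are the ones to use.

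**Arm versus leg.** A reader might want to add that the outcome pools the "targeted extremity (right or left arm or leg") without a limb term, and call that a second failure to respect the design. It is not one, because limb is not a matching factor. The ranges in section 2.13.1 (5.6–54.4% of daytime for the upper and 1.3–19.4% for the lower extremity) are movement levels. That section gives the spread of those levels as its reason for analysing percentage change: "Due to the wide variability in extremity movement among adolescents and young adults with CP at GMFCS-E&R levels I-V". Different levels do not show that limb predicts percentage change. The power gain from a limb term was about 1 point or less in simulation with baseline on the log scale. Randomisation with a valid standard error already allows for chance imbalance in limb.

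**Conclusion.** The point holds for age group and GMFCS-E&R level. The protocol balances on both factors and then fixes a primary model that ignores them. The consequence is a standard error that is too wide by an amount that depends on an unknown residual R². Under the assumptions above, including them gains nothing at R² = 0, about 3 power points at 0.1, about 6 at 0.2 and about 8 at 0.3. The omission of the factors is plain from the text, whereas the size of its effect is not.

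This is a near-free improvement that should be made. It does not threaten the validity of the trial or its sample size. Target limb is an optional precision covariate and no part of the defect.

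**What to change.** Add age group (15–19, 20–25) and GMFCS-E&R level as fixed effects to the model in section 2.13.3.1. Combine sparse levels, for example III–V, since 70% of participants are projected at I–II. Carry the same terms into the sensitivity models (section 2.13.5) and the secondary outcomes analysed by mixed model (section 2.13.3.2). The chi-square comparisons of attendance and adherence are unaffected.

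As section 2.6 describes them, pairs share nothing beyond their stratum, so the stratum factors are enough and a separate pair effect is not needed.

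Target limb (arm or leg), which is settled before randomisation, may be added as one further covariate, with a small expected gain.

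The cost is three degrees of freedom with GMFCS-E&R in three categories (one for age group, two for GMFCS-E&R), or four with limb. All the variables are recorded before randomisation. If the factors turn out not to matter, the simulated cost is about half a power point (81.0% against 80.5%). The change can go into the statistical analysis plan, which is still to be uploaded under section 2.13, and be declared with its reason as section 2.16 provides.

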### Trial design

2.1

This is a two-arm parallel assignment randomized clinical superiority trial in which adolescents and young adults with CP self-administer home-based motor training with or without Music Motion Feedback. Outcomes will be assessed before randomization, after 12 weeks of intervention (end of intervention - T2), and to evaluate the sustainability of potential improvements after 24 weeks (follow-up - T3). The trial design is visually presented in Fig. 1.

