#### Sample size

2.13.2

The sample size calculation is based on a systematic review and meta-analysis of controlled trials assessing extrinsic feedback on recovery and motor learning in individuals with brain injuries. The analysis found a significant Standardized Mean Difference of 0.76 with participants in identical motor training programs, differing only in feedback provision [16]. With 58 participants, we will attain a statistical power of 81.8 %. To account for potential dropouts, we plan to enroll 70 participants (35 in each group).

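### The primary mixed model puts a random intercept, a random slope and a residual on two change values per participant, so its variance components are not identified unless the intercept-slope covariance is constrained

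*Protocol article*

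**What the plan says.** All of the following is in the protocol article, section 2.13.3.1 (The primary outcome), unless noted.

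- The response is "percentage change in real-world targeted extremity movement from baseline (T1) to 12 weeks (T2) and 24 weeks (T3").
- The fixed part: "The model will include fixed effects for Group (Music Motion Feedback vs. Control"), then "Time (T1-T2, T1-T3), and their interaction (Group × Time), adjusted for baseline extremity movement time and sex". Baseline is a covariate and not a response row.
- The random part has two terms. On the intercept the plan says: "A random intercept for each participant will account for individual differences in baseline differences". Its second term is described in these words: "a random slope for Time will model variability in improvement rates". A residual is implicit in any linear mixed model.
- Estimation: "the analysis will be conducted using restricted maximum likelihood estimation".

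No structure is given for the covariance of the random effects. The trial design section (2.1) confirms one baseline and two later assessments. Section 2.10 makes T2 the primary endpoint. Section 2.13.3.2 applies the same approach to the secondary outcomes other than attendance and adherence.

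**The concern.** A random intercept, a random slope and a residual form a growth-curve structure. It suits raw values at three or more times, and the reasons given for the two random terms (differences between participants at baseline, differences in rate of improvement) read as if written for such a model. Here it is attached to change scores at two times, with baseline already used as a covariate. Two values per person do not hold enough information to separate the three sources of variation and the intercept-slope covariance.

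At stake is whether the primary analysis runs as written. If the software refuses it, a term has to be dropped or constrained, and the article does not say which. If it runs, the reported variance components have no meaning.

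A related gap is that the article names T2 as the primary endpoint but does not say which model term or contrast delivers the primary estimate. With a change-score response that is not the term many readers would look at first.

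**Working it through.** **The plan's own figure.** The only figure nearby is the power statement: "The analysis found a significant Standardized Mean Difference of 0.76", with 58 participants and 81.8 % power. At 29 per arm and two-sided alpha 0.05 (assumed; not stated for the sample size), the normal approximation gives 0.76 × √(29/2) − 1.96 = 0.934, a power of 82.5 %. The noncentral t gives 81.2 %. The figure is reproduced and this point does not affect it.

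**Counting parameters.** Code Time as 0 (T2) and 1 (T3). Let s0 be the intercept variance, s1 the slope variance, c their covariance and se the residual variance. Then:

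- Var at T2: V11 = s0 + se
- Var at T3: V22 = s0 + 2c + s1 + se
- Covariance: V12 = s0 + c

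That is three equations in four unknowns. Replacing (s0, c, s1, se) by (s0 + d, c − d, s1 + 2d, se − d) leaves all three unchanged for any d that keeps the variances valid.

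**Example** (illustrative values):

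| s0 | c | s1 | se | V11 | V22 | V12 |
|---|---|---|---|---|---|---|
| 400 | 0 | 100 | 200 | 600 | 700 | 400 |
| 500 | −100 | 300 | 100 | 600 | 700 | 400 |

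Both are valid random-effects matrices (second row: 500 × 300 − 100² = 140,000 > 0).

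**Other codings.** The rank of the derivative matrix of (V11, V22, V12) with respect to the parameters was:

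| Time coding | Correlated random effects (4 parameters) | Uncorrelated (3 parameters) |
|---|---|---|
| 0/1, 1/2, 12/24 | 3 | 3 |
| −0.5/0.5 | 3 | 2 |

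So the correlated model is never identified. The uncorrelated one is just identified except under centred coding. Raw values at three times with a linear slope would give rank 4, but that is not the stated model.

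**Simulated data** (70 participants × 2 values; assumed covariance V11 = 400, V22 = 500, V12 = 240).

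- First data set: the REML log-likelihood was −470.737657 with the residual variance fixed at about 0, 25, 50, 100 or 150. The T2 effect (4.439) and its SE (4.698) did not move. Between the ends, (s0, c, s1) went from (383.59, −235.39, 469.17) to (233.59, −85.39, 169.17), which is the shift above with d = −150.
- Second data set, fitted in standard software:

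| Model | T2 group effect | SE |
|---|---|---|
| lme4, correlated intercept and slope | refused: 140 observations, 140 random effects | – |
| nlme, correlated intercept and slope | 10.015 | 4.473 |
| lme4, uncorrelated intercept and slope | 10.015 | 4.473 |
| Unstructured 2×2 covariance, no random effects | 10.015 | 4.473 |
| Random intercept only | 10.009 | 4.540 |

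The nlme fit could not give intervals for its variance components.

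**Missing values.** A participant with one post-baseline value adds nothing to the covariance. Multiple imputation (section 2.13.4) restores two values each, so the count is the same in every imputed data set.

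**Which term is the treatment effect.** Let D2 and D3 be the group differences in percentage change at T2 and T3. With 0/1 coding the Group coefficient is D2 and Group × Time is D3 − D2. If the benefit is equal at both times, the interaction is zero however large the benefit. The Group coefficient also depends on coding: it is (D2 + D3)/2 under −0.5/0.5, and 2 × D2 − D3 under 12/24.

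**The case against.** The strongest reply is that nothing of consequence is wrong with the result. The 2×2 marginal covariance is identified even though its split is not, so any fit that converges gives the same T2 effect and SE as an unstructured covariance. No hypothesis and no success criterion in the article rests on the variance components. This stands, and it limits the weight of the point. A reader might infer that the primary estimate would be biased or the trial left without a primary analysis; neither follows.

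Second, the article does not say that the random effects are correlated, and with zero covariance the model is just identified under most codings. That is correct. But the article does not state that constraint, and a freely correlated intercept and slope is the usual reading.

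Third, a reader might infer that the replacement model would be chosen after seeing results. The documents do not support this. Sections 2.13 and 2.13.5 promise a full analysis plan before the last participant's first visit, the statistician is blinded (2.7), and the allocation sequence is revealed only after the analysis (2.6). The alternatives also differed little in the simulated example: SE 4.540 against 4.473, a ratio of 1.015.

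Fourth, a reader might infer that the plan takes Group × Time as the treatment effect. No passage says so. The interaction is only listed among the fixed effects, and T2 is named as the primary endpoint. What remains is that the contrast should be named.

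The reply that such detail belongs in the analysis plan does not dispose of the point. The article does not leave the random-effects structure open; it states one that two change values cannot support.

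**Conclusion.** The point holds in a limited form. As written, and unless the intercept-slope covariance is constrained, the primary model has four variance parameters for three covariance elements. Its variance components are not identified, and at least one standard package refuses it. The same applies to the secondary outcomes analysed in the same way. Where a fit is obtained, the treatment estimate and its standard error are not distorted.

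This rests on the stated response (change at two times, baseline as covariate) and on the usual correlated random effects. The rank result is algebraic and does not depend on the simulated values; the SE comparison comes from one simulated data set with an assumed covariance. Severity is moderate: a specification error in the primary analysis that wording can correct.

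**What to change.** In section 2.13.3.1, and in the statistical analysis plan:

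1. Remove the random intercept and random slope. Fit a repeated-measures model by REML with an unstructured 2×2 residual covariance for T2 and T3. This has three parameters for three covariance elements.
2. Keep the fixed effects already planned: Group, Time (T2, T3), Group × Time, baseline extremity movement and sex.
3. State that the primary estimate is the Group difference in percentage change at T2, obtained as a named contrast so that it does not depend on how Time is coded. State that Group × Time describes only how the group effect differs between T3 and T2.
4. Apply the same model to the secondary outcomes that section 2.13.3.2 assigns to the mixed-model approach.

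A baseline × Time term and Kenward-Roger degrees of freedom are optional; the identification problem does not require them. The cost is wording only, with no change to sample size, visits or data collection.

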#### Secondary outcomes

2.10.2

The secondary outcomes will evaluate changes in capacity and function. Participants will be split based on goal-directed training for upper or lower extremities. The effects of upper-extremity training will be assessed using the Action Research Arm Test (ARAT) total score, isometric arm strength, and maximum grip strength. For lower-extremity assessment, the Gross Motor Function Measure-66 (GMFM-66), isometric leg strength, and the 6-min walk test will be applied. In addition, attendance and adherence will be monitored as process measures.

**ARAT** consists of 19 items across four dimensions: grasp, grip, pinch, and gross arm movement. Each item is rated on a 4-point ordinal scale ranging from normal performance to inability to perform any part of the test. The maximum total score is 57 points, with higher scores indicating greater functioning [21].

A hand dynamometer will determine the percentage change in **maximum hand grip strength** (Jamar Technologies, Horsham, PA, USA). Participants will squeeze the device maximally. After one practice trial, three measurements will be taken, with rest periods. The highest value will be recorded as the maximum grip strength.

**GMFM-66** is a 66-item observational assessment divided into five dimensions: Lying and rolling, sitting, crawling and kneeling, standing, walking, running, and jumping. Each performance is rated on a 4-point ordinal scale: Does not initiate task, Initiates task (<10 %), Partially completes task (10–99 %), and Completes task (100 %). Calculations of GMFM-66 scores require the use of a computer program, Gross Motor Ability Estimator-3 (GMAE-3) [22].

**6MWT** measures submaximal aerobic and functional gait capacity. Able participants will walk 6 min on a 30-m walkway with the enclosed corridor length marked at every 3-m interval. Cones mark turnaround points. The total distance walked over the 6 min is used as the score [23].

**Isometric strength** will be assessed using handheld dynamometry by measuring maximal isometric force for muscle groups. Three measurements will be recorded with rest periods, and the highest value (kilogram force) per muscle group will be recorded as the maximum.

The TIA app will collect **attendance and adherence data**, which includes daily logins, session duration, and the time spent moving the targeted extremity.

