#### Statistical methods

2.13.3

The distributions of continuous data will be assessed using Quantile-Quantile (Q-Q) plots, histograms, and the Shapiro-Wilk test. Normally distributed continuous data will be analyzed with parametric statistics. If normality is not met, a logarithmic transformation will be applied. Ordinal data will use non-parametric statistics. Categorical data will be presented as frequencies and percentages. An intention-to-treat analysis will include data from all trial participants.

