##### Secondary outcomes

2.13.3.2

Attendance (number of training sessions) and adherence (active practice time) will each be categorized based on the prescribed dose achieved: low (<33 %), medium (33–66 %), and high (>66 %). Chi-square tests will compare the two groups' attendance distribution and adherence levels.

The analysis of other secondary outcomes will follow the same approach as the primary outcome, using LMM.

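### The log-transformation fallback for the primary model cannot be applied to a percentage change, which is zero or negative for every participant who does not improve

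*Protocol article*

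**What the plan says.** Section 2.10.1 (Primary outcome) defines the endpoint: "The primary outcome is the percentage change in real-world daytime movement of the targeted extremity". Section 2.13.3.1 makes that percentage change, from T1 to T2 and from T1 to T3, the response of the linear mixed model, "adjusted for baseline extremity movement time and sex". Section 2.13.1 (Superiority margin) gives the reason: because movement varies so widely between people, "percentage change was chosen over absolute change". It sets the margin at a 10% increase.

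The remedy for non-normality appears twice. The general rule in section 2.13.3 is "If normality is not met, a logarithmic transformation will be applied". For the primary model, section 2.13.3.1 says "If residuals indicate non-normality, a logarithmic transformation will be performed". Neither place names an offset, a follow-up/baseline ratio, a bootstrap or a rank-based method for the primary outcome. Section 2.13.3 also commits to an intention-to-treat analysis with data from every participant.

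For the secondary outcomes, section 2.13.3.2 says "The analysis of other secondary outcomes will follow the same approach as the primary outcome, using LMM". Section 2.10.2 states one of them as a relative change: "A hand dynamometer will determine the percentage change in" maximum grip strength.

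**The concern.** The response and its fallback are both fixed in the protocol, and they are incompatible. A participant who moves 20% less than at baseline has a response of -20, and one who does not change has 0. Neither has a logarithm. The rule therefore fails for exactly the participants who did not benefit.

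If the trigger fires, the analyst has two ways to stay close to the text. One is to keep only positive changes, which selects on the outcome after randomisation and breaks the intention-to-treat commitment. The other is to add a constant large enough to make every value positive. That constant would be chosen after seeing the data, and the 10% margin would no longer have a direct meaning on the resulting scale. Either way, the confirmatory analysis would rest on a decision that was not prespecified.

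**Working it through.** **Domain of the logarithm.** Let x be the percentage change.

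- x = -20 or x = -5: ln(x) is undefined.
- x = 0: ln(x) is minus infinity.
- The usual shift ln(1 + x), with x in percent, still fails at -5 and -20.
- The log of the follow-up/baseline ratio, ln(1 + x/100), exists for any decline short of zero movement: ln(0.80) = -0.223, ln(1.00) = 0, ln(1.20) = +0.182.

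Section 2.13.1 reports movement of 5.6% to 54.4% of daytime (upper limb) and 1.3% to 19.4% (lower limb). All these values are positive, so log movement exists over the reported range.

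**How many participants are affected.** The document gives no SD for percentage change or log movement, so the following are assumptions: test-retest SD s on the log scale at each occasion, no true change in controls, and a true 20% gain with feedback. The log ratio then has SD s√2, and

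- control: P(x ≤ 0) = 50%;
- feedback: P(x ≤ 0) = Φ(-ln 1.20 / (s√2)), with ln 1.20 = 0.182.

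| s | s√2 | Feedback | Both arms (mean with 50%) | Expected of 58 |
|---|---|---|---|---|
| 0.15 | 0.212 | 20% | 35% | 20 |
| 0.25 | 0.354 | 30% | 40% | 23 |
| 0.35 | 0.495 | 36% | 43% | 25 |

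The 58 is the analysed number in section 2.13.2 (29 per arm). The proportions differ between arms, so excluding these participants would be unbalanced as well as outcome-dependent.

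A second calculation takes percentage change itself as normal, with 35 per arm as enrolled. With mean +10%, 22% are at or below zero at SD 13.2 (10/0.76, the SD if 10 points equalled the planned standardised difference), 31% at SD 20 and 40% at SD 40. That is about 8 to 14 of 35. In the most favourable case tried (mean +20%, SD 13.2), the chance that nobody in an arm of 35 is at or below zero is about 10%.

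**How often the trigger fires.** Simulated trials used 29 per arm, half upper and half lower limbs, true movement spread over the reported ranges, and the model adjusted for baseline. The Shapiro-Wilk test, which section 2.13.3 names, rejected residual normality at the 5% level in about 35% of trials at s = 0.15, 68% to 69% at s = 0.25 and 90% at s = 0.35. The skew comes from the ratio: with a log-normal ratio of median 1.10 and log SD 0.4, percentage change has skewness of about 1.3.

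**Power, for completeness.** At s = 0.25, repeated simulations gave 46% to 49% for untransformed percentage change and 48% to 53% for log movement adjusted for log baseline. At s = 0.15 they gave 88% and 89%. The two are practically the same.

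**The case against.** The best defence is that the authors mean to log movement time or the follow-up/baseline ratio. That would be valid and would have essentially the same power as the model proposed here. The text never says so, however. It names percentage change as the response and then logs without naming another quantity. If this is the intention, the correction is short.

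It can also be said that the rule is conditional and that details belong in the statistical analysis plan. The condition is likely enough to matter. A later plan can add detail, but one that followed this text would inherit a rule that cannot be executed.

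A reader might infer several stronger claims that the document does not support:

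- **That the plan deletes non-responders.** It does not; the intention-to-treat commitment rules this out. A power of about 14% at s = 0.25 with only positive changes logged describes an analysis that the plan does not permit.
- **That a few participants with low baselines dominate the untransformed estimate.** Under constant log-scale noise, the size of the percentage change is unrelated to a person's true level (correlation about 0).
- **That noise in the baseline biases the treatment effect upward.** With no true change, the expected mean percentage change within an arm is exp(s²) - 1, which is 4.1% at s = 0.2 and 9.4% at s = 0.3. This applies to both randomised arms and largely cancels in the group contrast.
- **That all secondary outcomes share the defect.** Percentage change is stated only for grip strength. ARAT is given as a total score, and following the same approach may mean only the model class.

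**Conclusion.** The point stands in a limited form. The fallback in sections 2.13.3 and 2.13.3.1 is wrong as written, because it cannot be applied to the stated primary response for any participant with no change or a decline. That follows from the text alone and needs no assumption.

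The likelihood and extent do rest on assumptions: log-scale test-retest SDs of 0.15 to 0.35 and a true 20% gain with feedback. Over that range the trigger fires in about 35% to 90% of trials, and about 35% to 43% of participants have a change with no logarithm. The untransformed analysis is workable, and its power is not the complaint. The rule should be corrected before unblinding.

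**What to change.** 1. Prespecify the log of movement time, or of share of daytime, of the targeted extremity at T2 and T3 as the response, with log baseline replacing untransformed baseline as covariate. The log follow-up/baseline ratio adjusted for log baseline is equivalent: only the baseline coefficient changes, by 1.
2. Delete the residual-triggered transformation.
3. Back-transform the T2 group difference to a ratio. This keeps the relative effect that section 2.13.1 asks for.
4. Restate the 10% margin as a ratio of 1.10 (ln 1.10 = 0.095).
5. For grip strength, model the follow-up value with its baseline as covariate. A zero baseline has no percentage change, and the log fallback fails there for the same reason.

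The cost is more than wording. The estimand becomes a ratio of geometric means instead of a mean of percentages, the scale of the declared outcome and margin changes, and section 2.16 requires the amendment to be declared with reasons on the registry. Movement must be above zero, which the reported minimum of 1.3% of daytime supports. This is not the only sound remedy: a robust or bootstrap interval on untransformed percentage change, fixed in advance, would also remove the defect in the primary analysis. No new data collection is needed. No revised sample size can be derived, because the document gives no SD on either scale.
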